### Aim 1: effectiveness of UC DPP

To assess the effectiveness of the UC DPP Initiative, we will examine mean percent weight change from baseline at 12 month follow-up and 24 month follow-up within and between three groups of overweight/obese UC beneficiaries. Group 1 includes overweight/obese beneficiaries with documented prediabetes who receive UC DPP Initiative prediabetes awareness letters and enroll in DPP (i.e., receive “full treatment”). Group 2 includes overweight/obese beneficiaries with documented prediabetes who receive UC DPP Initiative prediabetes awareness letters, but do not enroll in DPP. Group 3 includes overweight/obese UC beneficiaries without documented prediabetes who are not included in the UC DPP Initiative (do not receive prediabetes awareness letters and do not enroll in DPP). Group 3 serves as a control group to account for secular trends and/or concurrent programs that may affect weight change outcomes among UC beneficiaries (such as weight management services any overweight/obese UC beneficiaries may receive as part of routine care). The primary outcome will be % weight change at 12-month follow-up within those who received a “full intervention dose” (i.e., Group 1) and secondary outcomes will compare mean % weight change between UC beneficiaries (Groups 1 vs. 2 and Group 1 + 2 vs. Group 3).

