### Data collection & statistical analyses

To measure mean percent weight change, we will use EHR weights, which are collected similarly across UC health center visits, and DPP session weights for UC beneficiaries who enroll in DPP. Baseline covariate differences between those with and without attrition will be examined and we will then adjust for any covariates found to be significantly different (*p* < 0.05) between attrition groups in order to satisfy the Missing at Random assumptions of the mixed effects models. Because attrition could be a consequence of our primary outcome (i.e. weight) our missing data may be Missing Not at Random. In this instance we will utilize pattern mixture modeling to impute missing valuies. We will conduct within-subject analysis estimates of UC DPP Initiative effectiveness among those who received a “full intervention dose” (i.e., Group 1 prediabetes awareness letters and enrolled in DPP). For this primary analysis, we will use a mixed effects linear regression model to compare percent weight change within Group 1 subjects 12 and 24 months before DPP enrollment (pre period) and 12 and 24 months after enrollment (post period). Models for the trajectory of percent weight change will be specified with a random intercept for person with nested random slope for time from enrollment measured on a continuum. Average within-person between time-period (post vs. pre-enrollment) differences in the trajectory for % weight change will be modeled using a fixed effect interaction term of time-by-time-period to test for between time-period differences in the rate of % weight change. These models will be fit using a random intercept for person and random slope for time-period (post vs pre). A fixed effect of time-period will be used to estimate the average between time-period difference in % weight change adjusting for the corresponding length of time over which the change was observed. For both models, exploratory post-hoc analyses will also consider additional subject level covariates (age, gender, race, ethnicity, number of co-morbidities, number of DPP sessions attended, education level and years employed at the institution), as well as DPP site. Interactions of the difference over time (rates or mean levels) by these subject characteristics or site will also be explored to evaluate whether there is a differential benefit of the program for certain groups of beneficiaries (i.e., heterogeneity in treatment effect) and across sites. In the presence of statistically significant (*p* < 0.05) interactions, the models will be stratified so as to allow for potential heterogeneity in the covariates as well.

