
We will also compare outcomes between UC beneficiaries in Groups 1 vs. 2, a between-subject comparison, to estimate DPP effectiveness while holding the effect of the prediabetes awareness campaign constant across groups (both Group 1 and 2 receive prediabetes outreach letters). The mixed effects models mentioned above will be modified to examine between group differences in within-person change by incorporating an interaction term with Group membership. Similarly, we will compare outcomes in Groups 1 + 2 vs. Group 3, a between-subject comparison akin to an intent-to-treat (ITT) analytic approach since outcomes are being assessed among all UC beneficiaries with documented prediabetes eligible to receive the UC DPP Initiative in comparison to similarly overweight/obese individuals not exposed to the program. We will use propensity score matching to identify comparable overweight/obese beneficiaries with (Groups 1 + 2) and without (Group 3) documented prediabetes. The propensity score model will include baseline age, gender, race/ethnicity, BMI, and medical co-morbidities. Matching will be accomplished through use of the nearest-neighbor algorithm. Between group balance in the propensity scores and covariates will additionally be examined. While Groups 1 and 2 have an easily defined baseline for differentiating between pre- and post- diabetes awareness (i.e., enrollment or awareness letter date), Group 3 will have their baseline selected as corresponding to 12–18 months (or 24–30 months) prior to their most recent EHR entry.

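### The secondary Group 1 vs Group 2 comparison runs on two clocks (enrollment and letter date), so it holds the letter effect constant only if none of that effect arises before enrollment

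*Protocol article*

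**What the plan says.** All references are to the protocol article.

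- **Groups (Aim 1).** Group 1 members "receive UC DPP Initiative prediabetes awareness letters and enroll in DPP". Group 2 members "receive UC DPP Initiative prediabetes awareness letters, but do not enroll in DPP". The primary outcome is the 12-month change within Group 1. Group 1 vs Group 2 is a secondary outcome.
- **Clock in the primary model (Data collection & statistical analyses).** Group 1's periods are "12 and 24 months before DPP enrollment (pre period) and 12 and 24 months after enrollment (post period"), and the model has a "nested random slope for time from enrollment measured on a continuum".
- **Group 1 vs Group 2 (same section).** The same models are modified by adding an interaction with group. The stated purpose is to estimate DPP effectiveness while "holding the effect of the prediabetes awareness campaign constant across groups (both Group 1 and 2 receive prediabetes outreach letters").
- **Baseline (same section).** "Groups 1 and 2 have an easily defined baseline for differentiating between pre- and post- diabetes awareness (i.e., enrollment or awareness letter date").
- **Order of events (The UC DPP initiative).** The letter gives contact details for the local campus program, so for people recruited by it the letter comes before enrollment. No letter-to-enrollment interval is given.
- **Assumed effects (Sample size and power calculations).** The 12-month loss is taken as 2% in Group 2 and 0% in Group 3, with a target of 5% in Group 1. The Group 1 vs Group 2 difference is 3 points, with 90% power at 50 vs 500.

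**The concern.** The campaign effect is said to be held constant because both groups received a letter. Equal receipt is not enough for a model that contrasts a pre-period with a post-period: the letter must also sit at the same place on each group's clock.

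Here it does not. Group 1's dividing line is enrollment, which follows the letter. Group 2 has no enrollment date, so its dividing line is the letter. Any response to the letter in the weeks or months before enrollment is booked as pre-period in Group 1, while the same stretch of time is booked as post-period in Group 2. The article describes both dates as separating before from after awareness, but in Group 1 awareness began with the letter.

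At stake is the meaning of the group-by-period term. It is offered as a DPP effect net of the letter, but it would be the DPP effect minus a misplaced part of the letter effect.

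**Working it through.** **1. Inputs**

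- Letter effect L = 2 points (Group 2 assumed 2%, Group 3 assumed 0%).
- DPP increment D = 3 points (Group 1 target 5% minus Group 2's 2%).
- Sample sizes 50 and 500, two-sided alpha 0.05, independent-samples t-test (the plan's own simplification).
- The SD is not stated, so it is back-solved from the plan's figures.
- The lag g from letter to enrollment is not stated. It is assumed to be 1, 3 or 6 months.
- It is also assumed that enrollers respond to the letter as Group 2 does, and that L accrues linearly over 12 months and then stays flat. The share reached before enrollment is then f = g/12.

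**2. The plan's own power figures**

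With 50 vs 500 and the noncentral t distribution, a detectable difference of 2.5 points at 80% power implies an SD of 6.01. An SD of 6.01 gives about 92% power for 3 points. Solving instead from 90% power for 3 points gives an SD of 6.23. The two stated figures agree up to rounding, and an SD range of 6.0 to 6.24 covers both. At SD 6.0 the standard error is 6.0 × √(1/50 + 1/500) = 0.89.

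**3. Where the letter effect falls under the split clocks (12-month loss, in points)**

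| | Pre-period | Post-period |
|---|---|---|
| Group 1 (clock starts at enrollment) | fL | D + (1 − f)L |
| Group 2 (clock starts at letter) | 0 | L |

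- Post-only contrast: D + (1 − f)L − L = D − fL = 3 − 2g/12.
- Post-minus-pre contrast, which the group interaction targets: [D + (1 − f)L − fL] − [L − 0] = D − 2fL = 3 − 4g/12.

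**4. Results**

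| Lag g | f | Post-only contrast | Power, SD 6.0 to 6.24 | Post-minus-pre contrast |
|---|---|---|---|---|
| 0 | 0 | 3.0 | 90-92% | 3.0 |
| 1 month | 0.08 | 2.8 | 86-89% | 2.7 |
| 3 months | 0.25 | 2.5 | 77-80% | 2.0 |
| 6 months | 0.50 | 2.0 | 58-61% | 1.0 |

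No power is given for the last column. The plan's t-test and its implied SD belong to the post-only contrast, and the document gives no SD for a change-in-change.

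**5. Check with one clock**

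If Group 2 is dated from a pseudo-enrollment point with the same lag, its post-period loss is (1 − f)L and its pre-period loss is fL. Both contrasts then return D = 3.0 for every f.

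**The case against.** The strongest reply is that the split is inferred. The baseline sentence names two dates without assigning them to groups, and its purpose is to set Groups 1 and 2 apart from Group 3. The enrollment clock is written out for the within-Group-1 analysis, and the models are to be modified for the between-group comparison. A letter date exists in both groups, and a condensed article may leave index-date rules to the full plan. It is true that the assignment is not spelled out. Even so, the reused models run on time from enrollment, Group 2 has no enrollment date, and nothing says that Group 1 is re-anchored at the letter. The holding-constant statement is made outright, and the anchors as written do not deliver it.

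Three further replies stand and limit the point:

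- The lag may be short. At 1 month the post-only shift is only 0.17 points.
- The 2-point letter effect is a planning value for people who do not enroll. Its size and timing in enrollers are assumptions made here.
- The comparison is secondary, and at the lags shown the error runs against DPP, not in its favor.

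A reader might infer three stronger things. The first is that the whole letter effect lies in Group 1's pre-period. The documents do not support this: only the part arising before enrollment does. The second is that power falls to about 60% at 3 months and 20% at 6 months. Those figures put the doubled interaction shift into a test sized for the post-only contrast. The third is that Group 1 alone had to remain employed, insured and motivated. The documents do not show this: Group 2 also needs follow-up weights, and motivation to enroll is self-selection, a different problem from the clock.

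**Conclusion.** The point holds in limited form. Followed as written, the Group 1 vs Group 2 comparison does not hold the campaign effect constant unless no letter-related weight change occurs before enrollment, and nothing in the plan secures that.

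Under the assumptions above, lags of 1 to 6 months take the post-only contrast from 3.0 down to between 2.8 and 2.0 points. They take the pre/post interaction down to between 2.7 and 1.0 points. These are ranges over an unstated lag and not estimates of the actual bias. The direction at these lags is to understate the DPP effect.

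Severity: should be fixed. The defect is clear and cheap to repair, but it concerns a secondary outcome, and the documents do not support calling it fatal to the evaluation.

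**What to change.** State a single time zero for both groups in this comparison. There are two workable ways:

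1. **Letter date for both groups.** This needs no new dates. Its cost is less DPP exposure within 12 months, by an amount that depends on the lag. For illustration, if the DPP increment also accrued linearly over 12 months, the contrast 12 months after the letter would be 3 × (12 − g)/12, or 2.75, 2.25 and 1.5 points at lags of 1, 3 and 6 months. That shortfall reflects shorter exposure and not a misplaced letter effect.
2. **Pseudo-enrollment dates for Group 2.** Draw each member's lag from the pooled Group 1 distribution of letter-to-enrollment lags, and require that the member is still a beneficiary on that date. Sampling within campus and letter month is not practical with about 10 Group 1 members per site. The cost is a date-assignment step and the loss of Group 2 members who have left by the assigned date.

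Name one as the main version, keep the other as a sensitivity analysis, and report the observed lag distribution. If the clocks are not aligned, withdraw the statement that the campaign effect is held constant. Neither version removes self-selection into enrollment, which needs its own treatment. Both are changes to analysis wording and data preparation only.

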### The University of California Diabetes Prevention Program (UC DPP) initiative

The UC DPP Initiative has four key components; 1) identification of diabetes prevention as a system-wide goal, 2) a prediabetes awareness campaign targeting at-risk beneficiaries, 3) coordinated DPP implementation and delivery on every UC campus 4) coverage of DPP for all campus affiliates, including faculty, staff and students, at no cost. Each campus identified local champions, engaged key stakeholders, and signed a Memorandum of Understanding (MOU) with UCOP to receive funding for program implementation. The MOU outlined a commitment to the goals of the initiative, delineated guidelines for DPP delivery, and confirmed available resources. Funding to campuses was based on fixed costs of delivering a DPP cohort (i.e., not based on number of participants or program outcomes). Although the UC system could have easily continued to outsource DPP delivery (as many universities and workplaces do through their insurers), this initiative aimed to prioritize diabetes prevention as a highly visible system-wide goal that leverages university-based infrastructure and resources to implement all four key components. For example, campuses aimed to implement > 4 DPP cohorts in their first 2 years and then receive additional UCOP funding to add cohorts based on local demand.

The UC DPP Coordinating Center was established by UCOP/UC Health to support system-wide DPP activities. The UC DPP Coordinating Center assists UC campuses with all aspects of program delivery, including DPP coach training by UCLA-based certified master trainers and data management for DPP cohorts. Centralizing some activities, such as coach training, provides efficiency of scale (e.g., each individual campus is not required to spend time and money to train master trainers). The Coordinating Center leads monthly group calls with all UC campuses and individual calls with each campus as needed. Each UC campus is also registered with the National DPP (each campus has their own unique CDC organization number in order to be eligible for CDC recognition).

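### Group 3's baseline is counted back from its last EHR entry, so the secondary Groups 1+2 vs Group 3 comparison selects controls on a later record and leaves calendar periods unaligned

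*Protocol article*

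**What the plan says.** All references are to the protocol article.

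- **Purpose of Group 3** (Aim 1: effectiveness of UC DPP): "Group 3 serves as a control group to account for secular trends and/or concurrent programs that may affect weight change outcomes among UC beneficiaries". The same section makes 12-month percent weight change within Group 1 the primary outcome. Groups 1 vs 2 and Groups 1+2 vs 3 are secondary.
- **Time zero, Groups 1 and 2** (Data collection & statistical analyses): "Groups 1 and 2 have an easily defined baseline for differentiating between pre- and post- diabetes awareness (i.e., enrollment or awareness letter date").
- **Time zero, Group 3** (same section): "Group 3 will have their baseline selected as corresponding to 12–18 months (or 24–30 months) prior to their most recent EHR entry".
- **Matching** (same section): "The propensity score model will include baseline age, gender, race/ethnicity, BMI, and medical co-morbidities". Calendar date and campus are not listed.
- **Time axis of the trajectory model** (same section): "random intercept for person with nested random slope for time from enrollment measured on a continuum". The model for the mean difference between periods also adjusts for the length of the interval observed.
- **Attrition**: the same section grants that loss may be a consequence of weight. Sample size and power calculations applies a 20% loss allowance to all sample sizes, Group 3 included.

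**The concern.** The two sides of the comparison have clocks that run in opposite directions. Groups 1 and 2 are defined at a date and then followed. Group 3 is defined from the end of its record and traced back.

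This has two consequences. First, entry to Group 3 depends on something that happens after baseline, namely a further EHR entry 12–18 (or 24–30) months later. Second, Group 3's calendar window is set by each person's last contact, not by when letters went out or people enrolled. A control group meant to absorb secular trends and concurrent programs needs to be observed over the same calendar period as the group it controls for.

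Groups 1+2 vs Group 3 is the only planned comparison with people outside the initiative. It therefore carries any claim about the initiative as a whole.

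**Working it through.** **1. The plan's own figures.** Sample size and power calculations gives, at two-sided alpha 0.05, 80% power for 1.1% with 550 vs 500, 80% power for 2.5% with 50 vs 500, and 90% power for 3% with 50 vs 500. No SD is stated, so these figures cannot be reproduced independently. The SD can be back-solved from the two-sample t-test, approximately SD = difference / [(z for alpha + z for power) × √(1/n1 + 1/n2)]:

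- 550 vs 500: √(1/550 + 1/500) = 0.0618; 1.1 / (2.80 × 0.0618) gives SD about 6.35.
- 50 vs 500: √(1/50 + 1/500) = 0.1483; 2.5 / (2.80 × 0.1483) gives SD about 6.01.
- 50 vs 500 at 90% power: 3 / (3.24 × 0.1483) gives SD about 6.23.

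The figures agree roughly on an SD of 6.0 to 6.35. If the sample sizes are cut by 20% (440/400 and 40/400), the implied SDs are 5.68, 5.37 and 5.57. The illustrations below use 6.0 to 6.4 and the uncut sizes.

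**2. Selection on a later entry.** If baseline = last entry minus 12–18 months, an entry exists 12–18 months after baseline for every Group 3 member. The rule does not say that the entry contains a weight. In Groups 1 and 2 neither a later entry nor a weight is guaranteed. The planned remedies for attrition (covariate adjustment, pattern mixture models) act on people who are in the sample and then lost. In Group 3 this part of the selection happens before the sample exists, so they cannot reach it.

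Illustration, with the strength of dependence assumed: percent weight change is normal with SD 6.2, and 20% are lost under a logistic model in which larger change (towards gain) raises the odds of loss. Shift in the mean among those retained:

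| Odds ratio of loss per SD (assumed) | Shift, percentage points |
|---|---|
| 1.5 | −0.48 |
| 2 | −0.79 |
| 3 | −1.14 |

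If people who lose weight drop out more often, the signs reverse.

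**3. Calendar alignment.** Three places could align the periods, and none does. The baseline rule ties Group 3 to its own last entry. The propensity score has no date. The trajectory model's axis is time from enrolment.

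What still cancels: under a constant trend of r points per year, an 18-month interval carries r × 0.5 more than a 12-month one (0.25 points at an assumed r = 0.5). Adjusting for interval length removes that. A change or program specific to one calendar period does not cancel.

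**4. What a given bias would do.** With no true effect, bias b and SE = SD × 0.0618 (0.371 at SD 6.0, 0.395 at SD 6.4), the rejection rate is 1 − Φ(1.96 − b/SE) + Φ(−1.96 − b/SE):

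| Bias b (assumed) | SD 6.0 | SD 6.4 |
|---|---|---|
| 0.25 | 10.3% | 9.7% |
| 0.5 | 27.1% | 24.4% |
| 1.0 | 77.0% | 71.5% |

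The nominal rate is 5%. With 550 vs 500, a bias below the stated detectable difference of 1.1% is enough to mislead.

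**The case against.** The strongest reply is that the affected comparison is secondary, that the primary analysis is anchored at DPP enrolment within Group 1, and that every bias figure above rests on an assumption. All of that stands, and it limits the point. It does not answer it, because the Group 3 rule is stated outright and is not a detail left to another document.

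A reader might infer more than the text supports:

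- *That Group 3 removes no secular trend at all.* A constant linear trend cancels once interval length is adjusted for, and some windows may overlap by chance.
- *That Group 3 has complete follow-up against 80% elsewhere.* An entry is not a weight, and the 20% is a planning allowance, not an observed rate.
- *That the two sides lie years apart.* The Background dates the initiative from 2018, but the letters are undated and no data cut is given.
- *That Group 3's final weights are distorted by illness visits.* Nothing says so, and Group 2's weights also come from routine EHR visits.
- *That the intent-to-treat analogy fails because Group 3 excludes enrollees, although the initiative includes* "coverage of DPP for all campus affiliates, including faculty, staff and students, at no cost". That concerns the group definition, not the baseline date. The article claims only a resemblance to intent-to-treat and gives no count of such enrollees.
- *That Group 1 vs Group 2 is biased by the lag from letter to enrolment.* The article names two possible dates without assigning one to each group for that contrast, and gives no lag. The fair criticism is ambiguity: different clocks would be possible in a comparison meant "to estimate DPP effectiveness while holding the effect of the prediabetes awareness campaign constant across groups".

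**Conclusion.** The point holds for the secondary Groups 1+2 vs Group 3 comparison. The stated rule conditions controls on a later EHR entry, and nothing shown aligns their calendar period with that of the people they are compared with. Period-specific trends and concurrent programs are therefore not controlled, contrary to Group 3's stated purpose. Matching on the listed covariates does not repair either problem.

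Neither the size nor the direction of the bias can be determined from the documents. The shifts of about 0.5 to 1.1 points and the rejection rates above 5% are illustrations. They rest on an SD back-solved from the stated power and on assumed biases or loss mechanisms. The primary within-Group-1 analysis is unaffected. For Group 1 vs Group 2 the article is ambiguous about time zero; bias is not established.

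**What to change.** For Groups 1+2 vs Group 3:

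1. Give Group 3 candidates index dates drawn from the calendar distribution of the Groups 1+2 letter dates, for example by risk-set matching within campus and letter month. Assign the date first, then measure eligibility and the propensity covariates as of that date. Matching first and borrowing the partner's date would be circular, because baseline BMI and co-morbidities need an index date.
2. Use the letter date as time zero for all of Groups 1+2 in this comparison.
3. Follow all groups forward with the same 12- and 24-month weight windows, and do not require a later entry.
4. Handle missing follow-up in the same way in all groups.
5. State how a Group 3 candidate who later receives a letter or enrols is treated.

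For Group 1 vs Group 2, state one common time zero.

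The cost is mainly reprogramming of index dates in the EHR data on which the plan already relies; the article does not describe the extract, so this is a presumption. Some Group 3 members will then lack a follow-up weight, which the 20% loss allowance already covers. The planned sample sizes need not change.
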